1. OUTCOME MEASURMENT

**Measurements for all outcomes will be collected using an online data collection and management system. Participants who will not have regular internet access during the trial period will be given paper forms to fill out and be asked to return the forms by prepaid mail or in-person at the end of the trial period.**

- - 1. PRIMARY OUTCOME

No clear definition or measurement tool for fatigue exists. The main limitation of fatigue scales is that very few have evidence indicating what constitutes a minimum clinically important difference (MCID) or a reference score for the target population. As such, the vitality subscale of the generic health-related quality of life instrument, RAND-36, will be employed to assess fatigue. The instrument will be administered at baseline, the end of each week (days 7, 14, 21, 28, 35, and 42). Since the vitality scale is not specifically validated for measuring fatigue, a Visual Analogue Scale for Fatigue (VAS-F) (44) will be concurrently administered so it can be compared to the vitality subscale since the VAS-F has proven validity in fatigued and healthy populations (45).

- - 1. SECONDARY OUTCOMES

1. ***Health-related quality of life:*** The RAND-36 is a 36-item questionnaire that assesses eight areas of functioning: physical functioning, role limitations caused by physical health problems, role limitations caused by emotional problems, social functioning, emotional well-being, vitality, and general health perceptions. This questionnaire will be assessed concurrent to the primary outcome (baseline, days 7, 14, 21, 28, 35 and 42) since the vitality subscale is a subset of this questionnaire.
2. ***Individualized outcomes:*** Since fatigue is subjective, and its impact is highly variable between individuals, individualized improvement will be measured using the Measure Yourself Medical Outcomes Profile (MYMOP). This tool will be used to measure change in items of importance to the participant, as identified by the participant. Participants will be asked to complete this short survey daily. Additional questions regarding concurrent medication and sleep hours/quality will be included on the MYMOP. On MYMOP for Day 1, participants will be probed as to their beliefs about which medication they have received in order to test the effectiveness of blinding.
   1. ***Beliefs about efficacy:*** At the beginning of the study, simultaneous to testing the effectiveness of the blind on day 1, participants will be asked how likely they think *R. rosea* is to be effective for fatigue. Participants will be asked the same question at the end of the study.
3. ***Adaptive capacity:*** The Adaptive Capacity Index (ACI) is a 21-item questionnaire that is intended to measure a subjects’ ability to adapt to stressors. The measure has recently been developed and this study aims to provide additional psychometric data about the measure. It is a self-reported measure comprised of five subscales measuring muscle endurance, cognitive function, sleep quality, emotional reactivity and social interaction. It will be administered on the same schedule as the primary outcome.
4. ***Adverse Event Monitoring:*** The daily MYMOP questionnaire has been adapted to query the participant on adverse events within the last 24 hours. A daily report of this item will be sent to the project coordinator once every 24 hours; if adverse events are reported, the study nurse will be notified to follow-up with the participant(s) by phone within 24 hours. For participants completing paper forms, the study nurse will follow-up once per week via phone call to collect information on adverse events. Nurses will record the nature, severity and duration of the adverse event(s). When serious adverse events are reported (i.e. those warranting physician visits or hospitalization), the study nurse will notify the data and safety monitoring board (DSMB). The DSMB will consist of a clinician, a trial methodologist and someone with natural health product expertise who are independent of the trial. In the event of an adverse event, the study nurse together with the qualified investigator may remove a participant from the trial. If the event(s) warrant it, the DSMB is empowered to stop the study prematurely**.** Subjects will also be contacted by phone once every 2 weeks by the study nurse to be queried about adverse event(s) that were not reported. Participants not participating in online electronic data collection will be asked to contact the study nurse within 24 hours of an adverse event occurring. All adverse events will be followed by the study nurse until resolution of baseline status is achieved or until the completion of the trial (i.e. when ethics approval has expired). We will ensure that Health Canada is informed of all serious adverse events within one week of occurrence.

Adverse events are defined as:

- Any untoward medical occurrence in a patient or clinical investigation subject administered a pharmaceutical product and which does not necessarily have to have a causal relationship with this treatment.

Serious adverse events are defined as:

- any untoward medical occurrence that at any dose:
  - results in death
  - is life-threatening, (NOTE: The term "life-threatening" in the definition of "serious" refers to an event in which the patient was at risk of death at the time of the event; it does not refer to an event which hypothetically might have caused death if it were more severe.)
  - requires inpatient hospitalisation or prolongation of existing hospitalisation,
  - results in persistent or significant disability/incapacity
  - is a congenital anomaly/birth defect.

A serious adverse event will result in withdrawal from the trial.

On the third study call, the study nurse will schedule a visit with subjects for the end of their 10-week clinical rotation. During that visit subjects will be asked to return all unused study medication, queried about occurrence of any adverse events after the end of the study period and asked about the effectiveness of study medication.

- - 1. WITHDRAWALS/Stopping rules

Due to the implied high prevalence of fatigue among nurses on shift-work, and anticipated low-risk of side-effects, a high rate of participant withdrawals is not expected. Nonetheless, a 40% drop-out rate has been accommodated in the sample size calculation.

Some participants may choose to withdraw from the study. Reasons for withdrawal will be documented as one of the following:

- Adverse Event (serious or not)
- Death
- Withdrawal of consent
- Protocol violation
- Treatment failure or insufficient response
- Lost to Follow up
- Other

Up to 2 attempts to contact participants who are lost to follow-up will be made by phone or email. Patients who withdraw from the study will be encouraged to undergo all outcomes assessments listed for the final follow-up session.

Those participants, who meet any of the exclusion criteria during the trial, will be withdrawn.

Since there will be no interim analysis performed, there are no stopping rules for the entire trial (i.e. for harm, benefit or lack of overall benefit of the intervention).

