All participants will begin the study on the same, fixed date when their shift work begins (date to be finalized in January 2011). Since data collection will be electronic via the internet, study participants are expected to have internet access. If participants know they will not have internet access or reliable access, arrangements will be made to give them either paper or offline electronic data collection forms (as well as a pre-paid envelope to send the forms back in).

- - 1. STUDY VISITS, phone calls and email reminders

In addition to the initial study visit and phone calls described in section 5.1.1., the project coordinatorwill phone each subject within 3 days of the study start to review study procedures and outcome assessment documentation procedures. At this time, the project coordinator will inquire about effectiveness of the blind and about participant beliefs about medication effectiveness. The next call from the project coordinator to participants will occur during the 2nd week of the study (days 14 to 20) inquire about adverse effects and to remind them of completion of the outcome assessment forms to be filled out~~.~~ The project coordinator will call study participants during the 5th week of the study (days 35 to 41) to remind them of the forms to be filled out, inquire about adverse effects and schedule a follow-up visit for when they are finished their clinical rotation at the end of 10 weeks. Throughout the study, subjects will also receive daily email reminders containing a link to the online data collection forms for that day. At the 10-week mark (day 70), participants will be sent an email reminder to complete all outcomes assessment forms for the final time. At this time, they will again be queried about their thoughts on effectiveness of the study medication. They will then return any unused study medication to the study nurse during their final scheduled visit.

1. trial INTERVENTIONS

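### Participants whom the protocol itself withdraws are only encouraged to attend one undefined final session, so remaining weekly scores, and possibly the week-6 score, are not clearly requested (minor, cheap to fix)

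*Protocol*

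**What the plan says.** Two rules take randomised participants out of the trial automatically. Section 7.1.3 states: "Those participants, who meet any of the exclusion criteria during the trial, will be withdrawn". Under adverse event monitoring, section 7.1.2 states: "A serious adverse event will result in withdrawal from the trial". A third rule, also in 7.1.2, is discretionary: "In the event of an adverse event, the study nurse together with the qualified investigator may remove a participant from the trial". Neither section separates stopping the capsules from leaving the study.

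The provision for data after withdrawal is one sentence in 7.1.3: "Patients who withdraw from the study will be encouraged to undergo all outcomes assessments listed for the final follow-up session". No session of that name is defined.

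The data are needed for section 8.2. The primary analysis there is an intention-to-treat two-sample t-test of change in RAND-36 vitality from baseline to six weeks, supplemented by a linear mixed model over time. Section 7.1.1 schedules the instrument at baseline and on days 7, 14, 21, 28, 35 and 42, with the VAS-F alongside it.

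**The concern.** An intention-to-treat comparison needs outcomes from everyone randomised, including those who stop the product. Some exclusion criteria in section 4.2 could arise during six weeks of shift work and may be related to fatigue or to treatment: insomnia, a mental health condition, medication acting on the central nervous system, low blood pressure or significant dizziness. Withdrawing people for such reasons, and then asking for little further data, can make the missing scores informative.

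This is a matter of trial conduct, so it cannot be left to a statistical analysis plan. The t-test needs a week-6 score and the mixed model can use only scores that were collected. The check of missingness planned in 8.2 can describe the gap, but it cannot recover scores that nobody requested. Those who withdraw consent can only be encouraged. Those removed by rule may be willing to go on filling in forms.

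**Working it through.** **Step 1. Which session is meant?** The protocol supports three readings.

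| Reading | Support in the protocol | Week-6 score requested? | Later weekly scores requested? |
|---|---|---|---|
| Day 42 | 6.1 measures all outcomes at baseline and week 6; 7.1.1 ends the schedule at day 42; 8.2 analyses change to six weeks | Yes | No |
| Day 70 | 5.1.2: the coordinator is to "schedule a follow-up visit for when they are finished their clinical rotation at the end of 10 weeks"; "At the 10-week mark (day 70), participants will be sent an email reminder to complete all outcomes assessment forms for the final time"; "They will then return any unused study medication to the study nurse during their final scheduled visit" | No | No |
| Time of withdrawal | 7.1.3 does not say when the assessments are to be done | No, unless withdrawal falls at about day 42 | No |

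Day 42 has the best support. In addition, where 7.1.2 lists the content of the 10-week visit, it gives return of medication, adverse events and perceived effectiveness, and does not mention RAND-36. Day 70 stays arguable because 5.1.2 has all outcome forms completed then, and because the visit called a follow-up visit there is the 10-week one.

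**Step 2. Scores obtained with full compliance.** Input: 6 scheduled post-baseline scores (7.1.1).

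| Withdrawn | Day-42 reading | Day-70 reading | Time-of-withdrawal reading | Schedule continued to day 42 |
|---|---|---|---|---|
| Before day 7 | 0 + 1 = 1 of 6 | 0 of 6 | 0 of 6, plus one unscheduled score | 6 of 6 |
| Between days 21 and 28 | 3 + 1 = 4 of 6 | 3 of 6 | 3 of 6, plus one unscheduled score | 6 of 6 |

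On the day-70 reading the substitute score comes 70 − 42 = 28 days after the primary time point.

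**Step 3. Possible effect on the primary difference (illustration only).** The protocol gives neither the number of such withdrawals nor how those withdrawn would have scored. Suppose one person is missing from an arm of n and that person's change is d points worse than the mean of the others. The full-arm mean is then the completers' mean minus d/n, so a completers' t-test shifts that arm by d/n. Assume d = 5 to 10 points. The target difference of 6.5 is from section 8.1.

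- If 90 is the trial total (45 per arm): 5/45 = 0.11 and 10/45 = 0.22 points, which is 0.11/6.5 = 1.7% and 0.22/6.5 = 3.4% of the target.
- If 90 were per arm: 5/90 = 0.06 and 10/90 = 0.11 points, or 0.9% and 1.7%.
- If loss and shortfall are the same in both arms: 0.

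These figures apply to each net one-person imbalance between arms.

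**The case against.** The case for leaving the text alone is substantial. The outcome schedule and the analysis both end at day 42, and a day-42 assessment needs no visit because the forms are completed online or on paper. On that reading the primary time point is requested, and only intermediate scores for a supplementary model are missing. The mixed model keeps all scores from before withdrawal, reasons for withdrawal are recorded, and 8.2 will explore missingness and its correlation with adverse events. The affected group is narrow: screened healthy students over six weeks, with 7.1.3 not expecting many withdrawals of any kind. Most of this stands, and it limits the priority of the point. It does not define the session, and it does not supply the remaining weekly scores.

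A reader might infer more than the text supports:

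- *Withdrawn participants are dropped from the analysis.* The protocol does not say so. It states intention to treat and it does ask for some outcome data after withdrawal.
- *The week-6 score is always lost.* This follows only if day 70 or the time of withdrawal is meant, and day 42 is the better-supported reading.
- *Every adverse event forces removal.* Removal for a non-serious event is discretionary.
- *The 40% drop-out allowance measures these withdrawals.* It covers drop-out of every kind and gives no rate for removal by rule. A loss of power calculated from it would not describe this problem.

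**Conclusion.** The point holds as a weakness in follow-up after withdrawal. Whichever session is meant, the weekly scores between withdrawal and day 42 are not requested from people whom the protocol itself removes. Whether their week-6 score is requested depends on an undefined term. Bias in the primary comparison requires removal, or the shortfall of those removed, to differ by arm. The protocol fixes neither its direction nor its size. On an assumed shortfall of 5 to 10 points, and with 90 as the trial total, it is 0.11 to 0.22 points per net one-person imbalance, and so probably small if such withdrawals are rare. No material threat to the primary result is shown. Priority: minor, worth correcting because the change is cheap.

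**What to change.** In 7.1.2 and 7.1.3, state that a serious adverse event, a newly met exclusion criterion or another adverse event leads to stopping study product where clinically required. State that these participants are asked to continue the weekly RAND-36 and VAS-F through day 42 unless they withdraw consent. In the follow-up sentence of 7.1.3, replace the reference to a final follow-up session with day 42. No further sentence on analysis by assigned arm is needed, because 8.2 already states intention to treat.

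The cost is a few lines of wording and at most six further weekly form completions per person, through an online system that already sends reminders. Some scores will be collected off product, which is consistent with the stated intention-to-treat analysis.

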1. STATISTICAL CONSIDERATIONS
   1. SAMPLE SIZE JUSTIFICATIONS

Lack of an appropriate, standard, valid tool to measure fatigue has been a barrier to high quality fatigue research. Previous R. rosea has suffered the consequence of this. Since no previous studies of R. rosea used a validated outcome measure or presented data in a manner on which to base sample size, sample size was calculated using the effect size from a comparable study of ginseng on fatigue (a comparable product from the same therapeutic class, i.e. adaptogen) (46). Using a two sided, two-sample t-test, a sample size of 64 participants achieves 90% power to detect an absolute mean difference of 6.5 on the RAND-36 vitality subscale between those randomized to receive R. rosea versus placebo at 0.05 level of significance (two-sided test). Assuming a drop-out rate of 40%, the sample size is increased to 90.

- 1. STATISTICAL ANALYSIS

Analysis will be conducted by the Epidemiology Coordinating and Research (EPICORE) Centre at the University of Alberta.

All primary analyses will apply the intention to treat principles. All statistical tests are two-sided and tests will be evaluated against 0.05 level of significance. Estimates and corresponding 95% confidence intervals will be reported. The RAND-36 vitality subscore will be used as the primary indicator of the efficacy of *R.rosea*. To test the main hypothesis of the effects of *R.rosea* in reducing fatigue of nurses involved in shift work, the mean change from baseline to six weeks of the vitality subscore using RAND-36 will be compared between the *R.rosea* and placebo groups. This 2-sample t-test will be supplemented by additional analyses using rate of change outcome measure. Linear mixed model will be employed to test changes in the intercept and slopes of the treatment groups. This type of modelling accounts for the variability and correlatedness of the observations on the same participant. Despite the tendency of participants to miss testing occasions, the mixed model analyses can still evaluate any trajectories of change. Missing data will be checked for randomness and correlation with adverse events will be explored. Since RAND-36 vitality subscore is not validated for use in this specific population, correlatedness between it and a visual analogue scale for fatigue (VAS-F) will be tested. In addition, correlatedness between ACI, will be tested against the primary outcomes in order to establish further evidence of validity. RAND-36 physical and mental component scores will be analysed by testing their mean change from baseline to day 42 between treatment groups, as a secondary outcome. Mixed model analyses will be applied for testing change for VAS-F, RAND-36, ACI and MYMOP. Side by side graphs of the rates of change between treatment groups will be plotted at the exploratory and final stages of analysis. Examination of the effect of the covariates - concurrent medication, dose-related change, sleep, alcohol use and impact of specific rotation (rotating vs permanent shift-work), age and marital status will be analyzed using linear mixed regression models as secondary outcomes. SAS 9.1 (Cary, N.C.) will be used for data management and statistical models. SPSS (Michigan) or Splus/ R will be used for supplemental graphs.

Adverse events will be monitored daily. Rates of adverse events will be compared between the two groups using the chi squared test at baseline, day 21 and day 42 measurements.

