**The code for a patient will only be opened in an emergency, when it is necessary for a patient’s treatment to be disclosed. If a code is broken the investigator will inform the Study Director/Monitor and document the details of the reason in the patient’s case report forms.**

- 1. ALLOCATION CONCEALMENT

Participants will receive a sealed, serially-numbered opaque bottle containing the study medication or placebo depending on their randomised group assignment. They will be provided a six-week supply of their assigned study medication.

- 1. BLINDING

**The placebo capsule will have the same appearance, volume, weight, odour and taste as the *R.rosea* product so that neither the participant nor trial personnel know who is receiving which medication. The effectiveness of the blind will be assessed at the beginning of the study after a single dose via the MYMOP on Day 1. Participants will be asked to guess which medication they think they were allocated to.**

- 1. **CO-INTERVENTION AND CONTAMINATION**

**Since stimulant medications have been identified as potentially hazardous to combine with *R.rosea*, subjects being recruited will be considered ineligible for the trial if they are using such medication. As part of their daily questionnaires, participants will be asked to record any medication used (prescription, over-the-counter, or natural health product) and quantity of caffeine and alcohol consumption in the past 24 hours to ensure that important co-variables can be considered in the final analysis. These questions will be administered as part of the daily MYMOP assessment.**

**From the start of the treatment, participants will be advised not to take any rhodiolaor ginseng preparations for the duration of the trial so that only the *R. rosea* treatment will influence trial outcomes. Furthermore, they will be informed that there is a 50% that they may be receiving *R.rosea*, the dose of which is being in this trial is the highest that has been supported by evidence of safety, and cautioned that they would therefore not want to “double-dose” themselves.**

- 1. **ACCOUNTABILITY OF TRIAL MEDICATION**

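### The drop-out allowance multiplies 64 by 1.4 instead of dividing by 0.6, so 90 participants give about 84% power, not 90%, if drop-out reaches 40%

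*Protocol*

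**What the plan says.** Section 8.1 specifies the test ("Using a two sided, two-sample t-test"), the significance level ("at 0.05 level of significance (two-sided test") and the target: "a sample size of 64 participants achieves 90% power to detect an absolute mean difference of 6.5 on the RAND-36 vitality subscale". It then allows for losses: "Assuming a drop-out rate of 40%, the sample size is increased to 90". No other basis for 90 is given.

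Section 7.1.3 says that few withdrawals are anticipated, and adds that "a 40% drop-out rate has been accommodated in the sample size calculation".

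Section 8.2 makes the same t-test the main analysis: "the mean change from baseline to six weeks of the vitality subscore using RAND-36 will be compared" between the groups. A linear mixed model is supplementary.

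No SD is printed. On its source, section 8.1 says that "sample size was calculated using the effect size from a comparable study of ginseng on fatigue".

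**The concern.** Sixty-four is the number that must be available for analysis. A 40% drop-out rate applies to the number randomised, so the number to randomise is 64 divided by the fraction retained. The protocol instead adds 40% of 64 to 64. This falls short, and the gap widens as the assumed drop-out rises; at 40% it is large enough to notice.

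What is at stake is the power claimed for the primary comparison. A reader of 8.1 and 7.1.3 would take the trial to keep 90% power even if 40% of participants were lost. If such a loss occurred and the result were null, the trial would be credited with more power than it had. The validity of the test and its type I error are not affected.

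**Working it through.** **Inputs**

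- Evaluable number 64, power 90%, difference 6.5 points, two-sample t-test, two-sided 0.05: section 8.1.
- Drop-out 40%, number to randomise 90: section 8.1, with the 40% repeated in 7.1.3.
- Equal allocation: inferred from section 6.6, where participants are told they have a 50% chance of active treatment.
- 64 and 90 are read as totals, which is the natural sense of the wording. Other readings are checked below.

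**Reproducing the plan's figure**

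n × (1 + d) = 64 × 1.40 = 89.6, rounded up to 90. This matches.

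**The number that covers 40%**

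n / (1 − d) = 64 / 0.60 = 106.7, so 107, or 108 for equal arms. That is 17 or 18 more than 90.

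**What 90 leaves**

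90 × (1 − 0.40) = 54, or 27 per arm, which is 10 short of 64. The largest drop-out that still leaves 64 is 1 − 64/90 = 26/90 = 28.9%.

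**Power with 54 evaluable**

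1. Find the standardised effect δ at which 32 per arm gives exactly 90% power (noncentral t, 62 degrees of freedom, noncentrality δ × √(32/2)). The solution is δ = 0.823.
2. Apply the same δ to 27 per arm: noncentrality 0.823 × √(27/2) = 3.02, 52 degrees of freedom. Power is 84.3%, so type II error is 15.7%.
3. Check by the normal approximation: Φ((1.960 + 1.282) × √(27/32) − 1.960) = 84.6%.
4. If the stated 90% was rounded from anything between 89.5% and 90.5%, power at 27 per arm lies between 83.7% and 85.0%.

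The SD does not enter: 64 and 90% fix δ, and δ carries over to the smaller number. In points, the difference detectable with 90% power rises from 6.5 to about 7.1.

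**Power with 90 randomised, by drop-out**

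| Drop-out | Evaluable | Power |
| --- | --- | --- |
| 10% | 81 | 95.5% |
| 20% | 72 | 93.1% |
| 28.9% | 64 | 90.0% |
| 35% | 58.5 | 87.2% |
| 40% | 54 | 84.3% |

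**Other readings of 64 and 90**

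- Both per arm: 54 per arm remain, and power is again about 84%.
- 64 per arm but 90 in total: power at 40% loss would be about 55%. The wording does not support this reading.

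Neither reading makes 90 correct.

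**The case against.** The best defence is that 40% is a safety margin and not a forecast. Section 7.1.3 expects few withdrawals, and at 10% or 20% loss the trial has more than 90% power. Withdrawn participants are also encouraged to complete the final assessments, so a withdrawal need not mean a missing week-6 outcome. The mixed model in section 8.2 uses the weekly data, and confidence intervals are promised, which limits misreading of a null result.

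This stands as an argument about severity. It does not justify 90. The calculation rests on the t-test, the t-test is the main analysis, and the protocol itself chose 40% and says that it is covered.

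Two stronger readings are tempting, and the documents support neither.

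- A reader might infer that the trial simply runs a 16% type II error instead of 10%. That holds only if 40% of the week-6 outcomes are actually lost. Up to 28.9% loss, the type II error is 10% or less on the protocol's own assumptions.
- A reader might infer from the missing SD that the power claim as a whole is unsound, and try larger SDs to show much lower power. The protocol names its source, a ginseng study that is not available here, and nothing in the document points to a larger SD. The unprinted SD is a reporting gap that prevents the 64 from being checked. It adds nothing to the size of the inflation error.

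**Conclusion.** The statement is wrong as written. At the protocol's own 40% drop-out, 90 randomised gives 54 evaluable participants and about 84% power for a 6.5-point difference, some 6 percentage points below the stated 90%. Holding 90% would take 107 randomised (108 for equal arms).

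The conclusion assumes equal arms, 64 and 90 as totals, and the stated 64 and 90% power taken at face value. It needs no SD.

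Severity is moderate. The shortfall arises only when drop-out exceeds 28.9%, power stays above 80% even at 40%, and high withdrawal is not expected.

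**What to change.** Restate the end of section 8.1 along these lines: *64 evaluable participants in total give 90% power; randomising 90 keeps this for drop-out up to about 28% and gives about 84% power if drop-out reaches 40%.* Note beside it that covering 40% at 90% power would take 107 randomised, or 108 for equal arms.

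Correct the sentence in section 7.1.3 to match, so that it no longer says 40% has been allowed for in full.

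Add to section 8.1 the SD that the sponsor used, whether it is an SD of change or of week-6 scores, and its source. Back-solving from 64 and 90% power gives about 7.9 points (6.5 / 0.823), but this should not be entered as the trial's assumption, because the sponsor never stated it.

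The cost is a few sentences in 8.1 and one in 7.1.3, and a less favourable power statement at 40% drop-out. Restating needs no extra participants. If the sponsor prefers to cover 40% in full, the cost is 17 or 18 more participants; section 4.1 puts the recruitment base above 200.
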